# Stand-on ride-on power mobility devices for children with cerebral palsy: pilot study protocol for waitlist-control pre-post biomechanical changes

**DOI:** 10.3389/fped.2026.1761608

**Published:** 2026-03-12

**Keywords:** balance, cerebral palsy, clinical trial, early intervention, mobility, pediatric disability, power mobility device, waitlist control

## Abstract

**Background:**

Many children with cerebral palsy are often deprived of participation in life activities due to limited postural control and walking capabilities. Ride-on power mobility devices (PMD) allow for the self-generated, active control of mobility. A novel stand-on ride-on device may provide the additional support to maintaining upright posture to improve children's balance and lower extremity strength. This pilot clinical trial aims primarily to assess the feasibility of conducting a full-scale randomized controlled trial, including evaluation of recruitment, retention, adherence to the intervention, and variability in outcome measures. Secondarily, the study will explore biomechanical factors underlying potential changes in balance and mobility function following adapted stand-on PMD use in natural environments.

**Methods:**

Ten children will participate in this single-arm waitlist-controlled pre-post feasibility trial. Children 4–6 years old with spastic diplegia cerebral palsy (Gross Motor Function Classification System level III) will engage in the intervention with individually adapted stand-on PMD use for three months at home, neighborhood, and family places. Biomechanical assessment will take place at baseline (3 months prior to intervention), at pre-, and at post-intervention. Exploratory outcome measures include center of pressure variables, kinematic variables of full-body coordination, and lower extremity muscle co-contraction during gait, sit-to-stand, and balance tasks.

**Discussion:**

This pilot clinical trial is the first to evaluate biomechanical factors underlying changes in balance (static and dynamic) and mobility function after stand-on PMD intervention. By collecting key feasibility metrics and quantifying variability in biomechanical outcomes, this study will generate fundamental knowledge to guide the design of a larger, adequately powered trial that can validate PMD interventions in decreasing the lifelong burden of secondary medical conditions that emerge in this population due to impaired balance and limited mobility. Findings will also provide the empirical data supporting the follow-up grant application with larger-scale study design.

**Clinical Trial Registration:**

ClinicalTrials.gov, identifier NCT06455930.

## Introduction

Children's participation in life activities with family and peers plays a vital role in their physical and psychosocial development; however, many children with neurologic-induced physical disabilities are often deprived of such interactions given limited postural control (1, 2) and walking capabilities, leading to delayed development and reduced quality of life (3, 4). In the past ∼10 years, ride-on power mobility devices (PMD), such as the go-baby-go cars (5–8), have gained much public health attention. These devices allow for the self-generated, active control of mobility, spatial exploration, and socialization that many of these children need (9).

Significant improvements in qualitative measures involving several areas of development have been reported for children with impaired mobility from varying developmental disabilities when PMD interventions were provided (7, 10–14). In particular, work stemming from the Go-Baby-Go initiative has consistently demonstrated meaningful improvements in psychosocial outcomes, including participation, social engagement, and quality of life, in children receiving individually adapted ride-on mobility devices (6, 7, 14, 15). While seated ride-on PMDs provide the self-directed exploration in alignment with the child's optic flow, they do not provide the link between the novel motor behavior and sensory experience, i.e., the child is moving but not activating lower extremity muscles and receiving information from mechanoreceptors to maintain standing posture and manipulate balance demands. More recently, adapted stand-on ride-on PMDs (10, 16, 17) have provided the additional support to maintaining an upright posture, increasing lower-extremity loading and proprioceptive demands that are absent during seated mobility. Prior work indicates that task-specific standing interventions can improve both static and dynamic balance in children with cerebral palsy, as evidenced by reductions in center-of-pressure sway following three-month weight-shifting programs (18, 19). In parallel, functional standing activities have been shown to enhance lower-extremity muscle strength and endurance, which are critical contributors to postural control during gait (20, 21). Despite these promising findings, the biomechanical mechanisms underlying balance and mobility changes associated with stand-on power mobility interventions remain largely unexplored.

Besides the limited scope of case reports (6, 22, 23) and case series (8, 24, 25) for the seated PMD, literature has largely provided only qualitative outcomes after use of these devices. Although important to support feasibility of administering interventions with devices for young children with disabilities to support self-directed mobility and socialization (6, 7, 10, 15, 22), available data do not elucidate the effects of powered mobility intervention on sensory-motor impairments, such as postural stability and whole-body motor coordination during static and dynamic conditions. The biomechanical factors underlying the purported beneficial physical changes of using stand-on PMDs have not been explored and are yet unknown. Biomechanical analysis enables objective quantification of postural stability, whole-body coordination, and neuromuscular control by integrating kinetic, kinematic, and electromyographic measures, thereby enabling mechanistic characterization of how mobility-based interventions may influence balance and movement strategies (2). Understanding which biomechanical factors can be altered after PMD use, especially stand-on devices, will guide subsequent intervention work to enhance functional outcomes (26).

This manuscript describes a study protocol for a pilot feasibility clinical trial designed to generate needed preliminary data to support subsequent adequately powered randomized controlled trial (RCT). The study is not intended to test intervention efficacy, but rather it aims to characterize feasibility metrics and explore variability in biomechanical outcomes associated with adapted stand-on PMD use in children with cerebral palsy and limited walking and balance control. Lifelong disabilities resulting from cerebral palsy lead to increased healthcare costs and place additional strain on caregivers (27). Our long-term research goal is to develop and validate effective interventions that can enhance the quality of life for children with cerebral palsy and their families. This aligns with the missions of National Institutes of Health (NIH)'s Eunice Kennedy Shriver National Institute of Child Health and Human Development (NICHD) and National Center for Medical Rehabilitation Research (NCMRR) to advance fundamental knowledge about the nervous system and apply that knowledge to alleviate the burden of neurological diseases.

### Objectives

The objective is to describe the study protocol of a pilot feasibility clinical trial. In this foundational work, we will test the feasibility of administering to a cohort of children with cerebral palsy an intervention with individually adapted stand-on PMD for three months.

#### Primary objective

To determine the feasibility of conducting a future RCT evaluating adapted stand-on PMD in young children with cerebral palsy [Gross Motor Function Classification System (GMFCS) level III] by assessing recruitment rates, retention, adherence to intervention, and variability in key outcome measures.

#### Secondary (exploratory) objective

To descriptively characterize changes in biomechanical measures related to static balance, dynamic balance, and gait following three months of adapted stand-on PMD use, with the purpose of informing outcome selection and sample-size estimation for future trials.

## Methods

### Study design

This design of the presented study protocol adheres to the established definition of a pilot/feasibility study, as outlined by the CONSORT extension for pilot and feasibility studies. Additionally, given the pilot nature of this project (R03) and the population (4–6-year-old children) who can undergo spurs of physical maturation, we selected a waitlist control design in which a baseline evaluation is administered 3 months prior to the pre-intervention evaluation. This is performed to control for changes in the secondary outcome measures that are due to maturation and not the proposed intervention.

### Study setting

While assessments are performed in the biomechanics laboratory within the university, intervention will take place at the children's home, neighborhood, and familiar places where the individually adapted PMD can be used.

### Participants

Study inclusion criteria {10} include: 1) Diagnosis of spastic diplegia cerebral palsy, GMFCS level III (28); 2) between 4 and 6 years old (age band selected based on the benefits of early intervention (12, 24) and the age-limitation imposed from the size constraints of the PMDs (toy cars) selected for the intervention); 3) able to stand and to walk short distances (at least 10 meters) with or without external assistance; 4) physician medical clearance to participate; and 5) exhibit sufficient cooperation and attention so that simple verbal instructions can be followed. Potential participants will be excluded if they: 1) have notable orthopedic conditions (e.g., lower extremity amputation; recent hip surgeries or soft tissue lengthening); 2) inadequate vision to complete study's procedures safely; 3) serious/unstable cardiac conditions that prevent engagement in the Evaluation Sessions; and 4) any other factor that might hinder full participation in the study or confound interpretation of the results. Although we will aim to recruit children who are not receiving balance/walking-specific rehabilitation, children can be engaged in therapy sessions while taking part in the study. We will account for the type and amount of rehabilitation statistically to maintain rigor of research and to generate robust homogeneous findings to support the subsequent study.

Ten children will be recruited {15} from local rehabilitation programs. Although no sex-difference in balance performance has been reported for children with cerebral palsy at the age band of interest (29), smaller differences in trunk control have been reported for children with cerebral palsy ages 8–14 years (30) and typically developing children (31, 32). Thus, we will aim to recruit five boys and five girls since sex will be considered as a biological factor (33–35) in the statistical analyses of the subsequent larger grant application.

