### Relevant concomitant care permitted or prohibited during the trial

Given the period of participation of six months, children will be allowed to receive any standard care deemed necessary by their respective physicians without prohibition while taking part in the study. If a major, surgical intervention is to be scheduled, e.g., selective dorsal rhizotomy, we will discuss options with the parents whether the major intervention can be performed once the study is completed, or whether the intervention must be received prior to participation. Other procedures related to standard care are not prohibited.

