### Statistical treatment

Due to the pilot nature of this study, descriptive statistics will be used to summarize feasibility outcomes, including recruitment, adherence, and retention rates. Variability in biomechanical measures will be estimated using means, standard deviations, and confidence intervals to guide sample size calculations for a future RCT. Given the small sample size, formal hypothesis testing will not be conducted. Preliminary pre-post comparisons of biomechanical outcomes will be reported using effect sizes (e.g., Cohen's d) and confidence intervals. Statistical analyzes will be performed with IBM SPSS Statistics version 28.0 (IBM Co., Armonk, NY, USA).

An external biostatistician will be contracted to perform all statistical treatments and control for any potential observer bias. The biostatistician will also manage the dataset to adjust for any missing data. We envision the use of multiple imputation where necessary, with assumption that the mechanism of missing data points was missed at random.

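### The plan admits children in concurrent therapy on a promise of statistical adjustment that its descriptive analysis does not contain and ten children cannot usefully support

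*Protocol article*

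**What the plan says.** The Participants section states a recruitment aim, not an exclusion: the team would prefer children without balance- or walking-specific rehabilitation, but "children can be engaged in therapy sessions while taking part in the study". The next sentence gives the safeguard: "We will account for the type and amount of rehabilitation statistically to maintain rigor of research and to generate robust homogeneous findings". The section on concomitant care adds that "children will be allowed to receive any standard care deemed necessary by their respective physicians without prohibition while taking part in the study"; only scheduled major surgery is singled out, for a discussion of timing with the parents.

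The abstract gives the size and design: "Ten children will participate in this single-arm waitlist-controlled pre-post feasibility trial". Study design explains that the three-month wait before the intervention is there to control for maturation.

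Statistical treatment then sets out descriptive summaries. For the biomechanical outcomes it says "Preliminary pre-post comparisons of biomechanical outcomes will be reported using effect sizes (e.g., Cohen's d) and confidence intervals", and also "Given the small sample size, formal hypothesis testing will not be conducted". It names no therapy covariate, adjusted model or stratification by therapy. It also does not name a comparison of the change over the wait with the change over the intervention period.

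**The concern.** The two sections do not fit together. One loosens entry because a statistical safeguard will be applied. The other treats the same ten children as too few for formal inference and describes an analysis without the safeguard. A reader of the results could believe that therapy exposure had been dealt with when it had not.

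What is at stake is the use of the exploratory results. The secondary objective directs them to outcome selection and sample-size estimation for the future trial. If some children gain from therapy during the device period, that gain is reported as change associated with the device. If therapy varies between children, the SD of change includes that variation. Children are recruited from local rehabilitation programs, so concurrent therapy is likely to be common.

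**Working it through.** The plan gives ten children without a precision or power derivation, so there is no stated figure to reproduce. The documents give no therapy effect, therapy distribution or number of therapy types; those values below are assumptions.

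**1. What each comparison contains.** For one child:
- wait change (baseline to pre) = maturation + therapy gain in the wait interval
- pre-post change = device + maturation + therapy gain in the intervention interval
- difference between the two = device + (therapy gain in intervention interval − therapy gain in wait interval) + any difference in maturation

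Steady therapy cancels only in the third line, and then only if its effect is the same in both intervals. The analysis section names the second line, where both steady and changing therapy remain.

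**2. Degrees of freedom.** Regress a child's change on therapy amount (one term) and three therapy types (two terms). Residual df = n − 1 − number of terms.
- n = 10: 9 without covariates, 8 with amount, 6 with amount and type.
- n = 8 (0.80 × 10): 7, 6 and 4.

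**3. Precision of the therapy-amount slope**, in residual SDs of change per SD of therapy amount. Amount is taken as standard normal, types as assigned at random. Half-width = t(0.975, df) × median standard error.

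| n | Model | Median SE | t | 95% half-width |
|---|---|---|---|---|
| 10 | amount | 0.347 | 2.306 | 0.80 |
| 10 | amount + 3 types | 0.397 | 2.447 | 0.97 |
| 8 | amount | 0.397 | 2.447 | 0.97 |
| 8 | amount + 3 types | 0.480 | 2.776 | 1.33 |

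When the residual SD is estimated within each simulated sample, the median half-widths at n = 10 are slightly smaller, about 0.76 and 0.91 to 0.93. The three-type model could not be fitted at all in about 5% of samples of ten and 11% to 12% of samples of eight.

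**4. Effect on the mean change.** Assume a true slope of 0.5 and a mean therapy exposure of 0, 0.5 or 1 SD. (For a contrast of the two intervals, read this as the mean change in therapy.) Bias of the unadjusted mean = 0.5 × mean exposure. Half-widths are simulation medians, with adjustment for amount and three types.

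| Mean exposure | Unadjusted bias | Unadjusted half-width, n = 10 | Adjusted half-width, n = 10 | Adjusted half-width, n = 8 |
|---|---|---|---|---|
| 0 | 0 | about 0.77 | 0.78 | 0.98 |
| 0.5 SD | 0.25 | about 0.77 | 0.89 | 1.13 |
| 1 SD | 0.50 | about 0.77 | 1.18 | 1.52 |

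Adjustment removes the bias on average. In any one sample, the bias it is meant to remove is well inside the adjusted interval.

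**5. Size without a model.** If k of ten children gain g SD from therapy during the device period, the mean change moves by k × g / 10. For k = 1, g = 0.3 this is 0.03 SD; for k = 5, g = 1.0 it is 0.50 SD. The planned Cohen's d absorbs it.

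**6. Effect on the SD.** With slope 0.5 and unit SD of therapy amount, the SD of change rises from 1 to √(1 + 0.5²) = 1.12. A sample size proportional to the variance would rise by 25%.

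**The case against.** The strongest reply has four parts.

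**The method may be in an unseen analysis plan.** Ruling out hypothesis tests does not rule out adjusted or stratified estimation, and accounting for therapy could mean a per-child description. This stands for the choice of method. It does not rescue the claim of robust and homogeneous findings, because no further document can make ten children enough for it.

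**Imprecision is not bias.** This stands. A reader might infer that adjustment could not remove confounding, or that the slope half-width is the uncertainty of the device effect. Neither follows. The slope is a nuisance parameter, a one-covariate model can be fitted, and with no mean therapy shift the adjusted mean is about as precise as the unadjusted one (0.78 against 0.77).

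**The recruitment preference is sensible.** This stands too. Because each child is measured over a wait and an intervention interval, a reader might infer that only a change in therapy matters, and that the preference should give way to an entry rule on therapy change. The documents do not support that. The named comparison is pre-post, in which steady therapy does not cancel, so the preference targets a real confounder and dropping it could let more confounding in. Nor is planned therapy change wholly out of reach of the criteria: the fourth exclusion covers factors that could confound interpretation, although it is discretionary.

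**The consequence is limited.** The article says the study is not intended to test efficacy and calls the findings hypothesis-generating. If the future trial also permits usual therapy, an SD that includes therapy variation may suit its planning. Both points hold. The second requires that the mix be described, and the article describes no recording of therapy exposure.

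**Conclusion.** The concern holds as a conflict between a stated safeguard and the stated analysis, made worse by a sample too small for the safeguard to work with useful precision. At n = 10 the half-width on the therapy-amount slope is about 0.8 to 1.0 residual SD, and at n = 8 about 1.0 to 1.3. Depending on how many children gain from therapy and by how much, the pre-post effect size could shift by 0.03 to 0.50 SD. These sizes rest on assumed therapy effects and distributions. The conflict between the sections does not, and the lack of precision appears even in the simplest case, with amount as the only covariate.

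It should be corrected, but it does not threaten the trial. The variability criterion draws on the affected SDs, although a sample size could still be computed from them. A reader might infer that the feasibility conclusion is compromised; the other three progression criteria do not depend on therapy mix, so the documents do not support that.

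**What to change.** 1. In Participants, delete the sentence on statistical accounting and homogeneity, or limit it to a labelled descriptive sensitivity display. Keep the recruitment preference and the eligibility criteria as they are. Permitted care need not change.
2. Record therapy type and minutes per week for the wait interval and the intervention interval separately, for example by parent report at the pre- and post-intervention visits. The bi-weekly calls and the parent log are described only under the intervention protocol and device tracking, so they cannot be assumed to cover the wait.
3. In Statistical treatment, add the within-child difference between intervention-interval change and wait-interval change, reported beside the pre-post change.
4. List each child's therapy in both intervals next to that child's changes, and show the summary with and without children whose therapy changed between intervals.

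The cost is a short questionnaire at existing visits and a less favourable stated claim. The between-interval difference is also noisier. If variation were only independent measurement error with variance s² at each visit, post − 2 × pre + baseline has variance 6s² against 2s² for pre-post, so its SD is √3 = 1.73 times as large. That is why it should accompany the pre-post change and not replace it.

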### Intake screening and consent/assent procedures

Once potential participants contact us, the initial intake screening to confirm eligibility will be performed by the research team's physical therapist who has 30 + years of experience with evaluating and treating children with neurologic condition, including cerebral palsy. This intake, which takes place at the Laboratory of Applied Biomechanics and Engineering at the University of North Florida, involves assessment of each participants’ anthropometric measurements, range of motion, and muscle tone. Weight (kg) will be measured using a calibrated digital scale (Pelstar Professional Scale, model 349KLX, China) with participants standing independently when possible, or seated when standing is not feasible. Height (cm) will be measured using a wall-mounted stadiometer (Seca, model 264, Germany) with clinician assisting child to maintain a stand-up posture when needed. Following, with the child lying supine on a floor mat, lower-extremity and bilateral foot length (cm) will be measured using a tape measure; width (mm) of bilateral knees, ankles, and forefeet will be measured using a digital caliper. Passive range of motion will be assessed using a standard goniometer to measure joint angles accurately. Muscle tone will be assessed using the modified Ashworth Scale, which provides a reliable grading of spasticity levels in each of the joints of the participants’ extremities.

Once confirmed eligibility, parents and children will meet with the PI of the study ([name]) at a dedicated private room for the informed consent/assent procedures approved by the University's Institutional Review Board (UNF IRB LEG-2147539). A basic set of medical information will be reviewed to confirm participant's eligibility for the study and physician clearance for participation in the activities associated with the research study will be obtained. If a participant withdraws, we will document the reason for withdrawal and recruit a new participant to replace the individual who withdrew.

